### Aims and hypotheses

The study seeks to (1) assess the effectiveness of an annual oral health preventive intervention in slowing the incidence of dental caries in children in a remote, rural Indigenous setting, (2) identify the mediating role of known risk factors for dental caries and (3) assess the cost-effectiveness and cost-benefit of the intervention.

We hypothesise that 1 and 2 years after the intervention (1) the actual incidence of dental caries in children will be significantly lower than the expected incidence, based on modelling from the two oral health surveys conducted over the past 11 years in the same community, the current survey and (2) the intervention will be cost-effective and cost beneficial, and therefore feasible and sustainable for broader implementation across similar communities in Australia and internationally.

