### Study participants

All children (approximately 600–650) attending the two primary and one secondary school campuses will be invited to participate in the intervention study. These children will be 4–17 years of age, and almost all are Indigenous. As all children in the community will be invited to participate a sample power calculation was not performed.

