### Analysis

All baseline socio-demographic characteristics will be described for the selected sample using counts and frequencies. Baseline and follow-up caries experience and questionnaire related information will be reported. Dental caries increment (incidence) will be the main outcome measure used to determine the effectiveness of the preventive intervention. The expected caries increment will be modelled from the three oral health surveys conducted in this community (2004; 2012 and 2015) and compared with the actual caries increment from 2015–2016; 2016–2017 and 2015–2017. The mean caries increment will be compared between the expected (modelled) and actual findings, and adjusted for known risk factors for dental caries. The hypothesis will be that caries increment observed in the period of 2015 to 2017 is smaller than the modelled caries increments. Two independent samples *t*-test will be used for the analysis with significance being determined if *p* < 0.05.

Children who receive only a part of the intervention will be separately assessed: for example we will have children who fully participate, those with baseline and only a year 1 follow-up, those with baseline and only a year 2 follow-up. This will ‘naturally’ further inform us on the most appropriate frequency of this preventive strategy. Both a group and matched analysis will be conducted to account for children who receive only part of the intervention.

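### The two hypothesis statements name different time points, and three overlapping increments share one unadjusted p < 0.05 with none named as deciding

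*Protocol article*

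**What the plan says.** All places are in the protocol article.

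- **Analysis, main outcome:** "Dental caries increment (incidence) will be the main outcome measure used to determine the effectiveness of the preventive intervention".
- **Analysis, comparisons:** the expected increment from the model is to be "compared with the actual caries increment from 2015–2016; 2016–2017 and 2015–2017". That makes three comparisons on the main outcome.
- **Analysis, hypothesis:** that the "caries increment observed in the period of 2015 to 2017 is smaller than the modelled caries increments". Only one observed period is named.
- **Analysis, test:** a two-sample t-test, "with significance being determined if *p* < 0.05". No adjustment or ordering is given, and sidedness is not stated.
- **Aims and hypotheses:** "We hypothesise that 1 and 2 years after the intervention", it says, "the actual incidence of dental caries in children will be significantly lower than the expected incidence". Two time points are named, without saying whether either or both must succeed.

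The Primary outcome variable section says that caries is measured annually and names no primary time point, so it does not settle the matter.

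**The concern.** The article answers the question of which increment tests the hypothesis in three ways: one period (the hypothesis in Analysis), two time points (Aims) and three comparisons (the list in Analysis). No rule links them.

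Two things are at stake. First, the deciding period could be chosen after the results are seen, and a reader could not then tell whether a reported p < 0.05 carries a 5% error rate or a larger one. Second, the choice of period changes who is analysed. The Analysis section expects some children to have a baseline and only one of the two follow-ups. A child seen only at the first follow-up can contribute to 2015–2016 but not to 2015–2017, and a child seen only at the second does the reverse. With no control group and a modelled comparator, naming the deciding comparison in advance is a cheap safeguard.

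**Working it through.** **Inputs from the article.** Threshold 0.05 with no split (Analysis); three comparisons, the third spanning the first two (Analysis); two time points in the hypothesis (Aims and hypotheses). I take the two-year statement to mean the cumulative 2015–2017 increment.

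**Assumptions.** The article gives no correlation ρ between the year-1 and year-2 test statistics, so I use -0.5 to 0.9. Yearly variances are equal in the base case, and each t-test is taken to hold its nominal level.

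**The article's own figure.** If one comparison decides, the false-positive chance is 0.05, as stated.

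**Model for several comparisons.** Under no effect, let Z1 and Z2 be standard normal with correlation ρ. The two-year statistic is Z3 = (Z1 + Z2) / √(2 + 2ρ). Its correlation with each yearly statistic is √((1 + ρ)/2), which is 0.71 at ρ = 0 and 0.87 at ρ = 0.5. The chance that at least one statistic passes its critical value (1.96 two-sided, 1.645 one-sided) was found from 4,000,000 simulated draws per setting.

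| ρ | Any of three, two-sided | Any of three, one-sided | Either Aims time point (Z1 or Z3), two-sided |
|---|---|---|---|
| -0.5 | 0.122 | 0.126 | 0.091 |
| -0.3 | 0.121 | 0.120 | 0.088 |
| 0 | 0.115 | 0.110 | 0.083 |
| 0.3 | 0.105 | 0.100 | 0.078 |
| 0.5 | 0.097 | 0.092 | 0.074 |
| 0.7 | 0.086 | 0.082 | 0.068 |
| 0.9 | 0.071 | 0.068 | 0.060 |

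**Bounds.** Three independent tests would give 1 - 0.95³ = 0.143, and the Bonferroni sum is 3 × 0.05 = 0.15. The overlap keeps the true figure below both.

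**Unequal yearly variances.** With a year-2 to year-1 SD ratio of 0.7 or 2 and ρ = 0, the three-test two-sided figure is 0.114 or 0.112, hardly changed. The two-test figure moves more, to 0.077 or 0.092.

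**Favourable direction only.** The two-sided figures also count results showing more caries than expected. If only results in the hypothesised direction count, two-sided testing at ρ = 0 gives 0.058 against a nominal 0.025.

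**All must be significant.** The chance cannot exceed that of any single test, so it is at most 0.05.

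**After the fix.** One named comparison gives 0.05. For reference, 0.05/3 = 0.0167 for each of three tests also holds the total to at most 0.05 (1 - (1 - 0.0167)³ = 0.049 if they were independent).

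**The case against.** A reader might infer that the false-positive chance simply is about twice 5%. The article does not support that. It needs a rule that any one significant period counts as success, and the article neither states nor excludes such a rule. The hypothesis sentence in Analysis stands directly before the t-test and threshold, so the threshold can fairly be read as belonging to 2015–2017 alone, with error 5%. The Aims join the two time points with a plain conjunction; if both are required, the error is at most 5%. No hypothesis statement rests on 2016–2017 alone, which appears only in the list of comparisons. The article also claims no study-wide error rate.

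Three technical points also stand. One model supplies every expected value ("The expected caries increment will be modelled from the three oral health surveys conducted in this community"), which probably raises the correlation between the test statistics and pulls the figures towards the lower rows of the table. The two-year increment is exactly the sum of the yearly ones only for children examined at all three visits. And the two-sided figures include unfavourable results, which could not confirm the hypothesis.

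It can further be said that multiplicity is commonly left to an analysis plan, which is not shown here. That is a good answer to a complaint about a missing adjustment. It does not answer the conflict: which period the hypothesis concerns is stated twice in this article, and the two statements differ. A later plan would have to override one of them.

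**Conclusion.** The point holds as an inconsistency between two sections, with a conditional effect on the error rate. Aims and hypotheses names two time points; Analysis names one period for its hypothesis but lists three overlapping comparisons under one unadjusted threshold; nothing says which decides.

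The size depends on the success rule:

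- 5% if 2015–2017 alone decides;
- at most 5% if all must be significant;
- about 6–8% two-sided if either time point in the Aims suffices, for ρ of 0.9 to 0;
- about 10–12% two-sided if any one of the three counts, for ρ of -0.5 to 0.5, and about 7–9% for ρ of 0.7 to 0.9.

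These figures rest on assumed correlations, equal yearly variances and valid t-tests. Whether a t-test of observed against modelled increments holds its level is a separate question. Doubling of the error is thus one possible outcome of the ambiguity and not an established property of the plan. The conflict bears on the main claim and is easily removed, so it should be corrected.

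**What to change.** Use the same statement in Aims and hypotheses and in Analysis: the 2015–2017 increment, the period that the Analysis hypothesis already names, is the single primary comparison, tested at 0.05. Report 2015–2016 and 2016–2017 as secondary estimates with 95% confidence intervals, or test 2015–2016 only after 2015–2017 is significant. Requiring significance at both Aims time points would also hold 5%, but it is more demanding, and the article reports that "a sample power calculation was not performed".

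The cost is one or two sentences, with no new data. The downside is that a 1-year result alone can no longer carry the claim.

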## Methods

### Study design

This is a longitudinal preventive intervention study. All school children in the NPA will be invited to participate. As it is unethical to withhold any proven intervention from any child, no control group will be created. Children who do not consent to participate may be natural controls if they consent to a dental examination at the end of the study. The actual caries increment in the children who participate will be compared to the expected caries increment modelled on oral health surveys carried out in this community in 2004 (pre-water fluoridation); in 2012 (by the Griffith University team post-partial water fluoridation) and 2015 (baseline survey for this study).

All consenting children will undergo a detailed head, neck and dental clinical examination and complete a questionnaire on their basic demography (gender and age), residential history (exposure to fluoridated drinking water), own general and oral health perceptions; oral health behaviours, attitudes and knowledge; dental visits; diet and oral health-related quality of life.

All active disease will be treated prior to implementing the dental caries preventive intervention. In years 2 and 3 of the study, all participating children will be invited to return for a dental examination, treatment of new incident disease and repeat of the prevention regime.

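### The only named effectiveness test, a two-sample t-test of actual against modelled increments, ignores error in the modelled mean and cannot make the promised covariate adjustment

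*Protocol article*

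**What the plan says.** Under Study design, the protocol article states that "no control group will be created". In its place, "The actual caries increment in the children who participate will be compared to the expected caries increment", which is modelled on surveys of the same community in 2004, 2012 and 2015. That section identifies the 2015 survey as the baseline of the present study.

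Under Analysis, caries increment is the main outcome. Actual increments are taken over 2015-16, 2016-17 and 2015-17. The comparison is described as follows: "The mean caries increment will be compared between the expected (modelled) and actual findings, and adjusted for known risk factors for dental caries". The hypothesis is directional: "The hypothesis will be that caries increment observed in the period of 2015 to 2017 is smaller than the modelled caries increments". The test is then given: "Two independent samples *t*-test will be used for the analysis with significance being determined if *p* < 0.05". The Covariates section names the adjustment factors as oral hygiene behaviours and sugar consumption.

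Parameter uncertainty is carried through only under Cost utility analysis, which specifies 95% confidence intervals for probabilities and a probabilistic sensitivity analysis. Nothing comparable is attached to the effectiveness test.

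**The concern.** A two independent samples t-test assumes two separate sets of sampled individuals and takes its standard error from the spread and number of values in each. Here one set is model output. Three consequences follow from the text.

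- **Independence.** The 2015 survey helps to produce the expected values and is also the starting point of the 2015-16 and 2015-17 actual increments. If expected values are produced child by child, they also correlate with those children's observed increments.
- **Model error.** If the fitted mean is too high or too low, every prediction is wrong by the same amount. That shared error does not shrink as predictions are added, and the t-test cannot see it.
- **Adjustment.** A t-test has no covariates, so it cannot deliver the adjusted comparison promised in the same paragraph.

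With no control group, this test carries the whole effectiveness hypothesis. If its p-value is not calibrated, error in the modelled mean can be read as an effect of the intervention.

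**Working it through.** The article gives no SD, effect size, power or model error, so there is no figure of its own to reproduce. The calculation below is illustrative.

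**Inputs**

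- From the article: p < 0.05 (Analysis); about 600-650 children invited (Study participants); 339 children in the 2012 survey (Background).
- Assumed: SD of the increment 2.0; n = 450 children with one prediction each; predictions explaining a share R2 = 0.1 of the variance; a standard error of the modelled mean, SE_m, from 0 to 0.3; a two-sided test, since the article does not state sidedness.

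**Formulas, under no true effect**

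- Variance that the t-test uses: (SD² + R2·SD²)/n = (4 + 0.4)/450 = 0.00978, a standard error of 0.099 whatever the model error.
- True variance of the difference: (SD² − R2·SD²)/n + SE_m² = (4 − 0.4)/450 + SE_m² = 0.0080 + SE_m².
- The test rejects when the difference exceeds 1.96 × 0.099 = 0.194 in either direction. Type I error is 2·[1 − Φ(0.194 / true SE)].

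**Results**

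| SE_m | True SE | SE used by the t-test | Two-sided type I error |
|---|---|---|---|
| 0 | 0.089 | 0.099 | 3.0% |
| 0.05 | 0.102 | 0.099 | 5.9% |
| 0.1 | 0.134 | 0.099 | 14.9% |
| 0.2 | 0.219 | 0.099 | 37.6% |
| 0.3 | 0.313 | 0.099 | 53.6% |

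Simulation with 20,000 runs per scenario gave 3.0%, 14.9%, 36.7% and 53.3% at SE_m 0, 0.1, 0.2 and 0.3. At SE_m = 0.1, varying n over 300-600 and R2 over 0-0.3 gives 6.3% to 21.5%.

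**Direction.** The two variance faults oppose each other. With no model error, ignoring the correlation makes the test conservative: 3.0% at R2 = 0.1 and 0.8% at R2 = 0.3. Model error pushes the other way. Because that error can have either sign, false benefit is about half of each figure: at SE_m = 0.1, 14.9%/2 = 7.5%, against a benchmark of 2.5%.

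**Plausible SE_m.** Take one survey of 339 children, assume ages spread evenly over 4-17 (SD 4.03) and a caries-count SD of 2 to 4, and read a two-year increment off a linear age slope. SE_m = 2·SD/(√339 × 4.03), which is 0.054 at SD 2 and 0.108 at SD 4. This excludes any error from the time trend. The Background section reports a 37.3% fall in caries between 2004 and 2012, and fluoridation that ran erratically and stopped in April 2011, so that trend is hard to model.

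**Arbitrary second sample size.** If the expected values were simulated individuals instead, the p-value would depend on how many were drawn. With SD 2.0, 450 observed children and SE_m = 0.1, the t-test variance is 4/450 + 4/m and the true variance adds 0.01. Type I error is about 7% at m = 100, 12% at m = 450 and 18% for very large m.

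**The case against.** The strongest reply is that the article does not say what form the expected values take (predictions per child, simulated individuals or survey-based increments), and that model specification is commonly left to a full protocol or analysis plan. That is so, and it is why no single error rate can be claimed. It does not rescue the test: in each of these forms the error in the modelled mean stays outside a two-sample t-test.

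It can also be said that adjustment might sit inside the expected-increment model or in a further analysis. That is possible, and the text does not show that adjustment will be absent. But the article does not say so, nor whether the 2004 and 2012 surveys recorded oral hygiene and sugar consumption. The named test and the promised adjustment still have to be reconciled.

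A reader might infer more than the text supports:

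- **That the test must overstate significance.** It need not. With little model error it is conservative or close to nominal.
- **That skewed counts with many zeros invalidate it.** At several hundred children, a two-sided t-test on skewed counts holds close to 5% when the expected mean is known exactly.
- **That sibling clustering inflates the variance.** The article says nothing of siblings or households.
- **That three periods are each tested at 0.05.** The p-value sentence directly follows the 2015-2017 hypothesis. Some ambiguity remains, because Aims and hypotheses speaks of both 1 and 2 years.

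**Conclusion.** The point holds as a fault in the stated method. The planned t-test treats model output as an independent sample, leaves out the error in the modelled mean, and contradicts the promised adjustment, so its p-value is not calibrated. This is a wrong choice in the text rather than detail deferred to another document.

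The size is conditional. On the assumptions shown, type I error runs from below nominal (3%) with no model error to 15% at a model standard error of 0.1 and 38% at 0.2, and about half of any excess would appear as false benefit. A model standard error of 0.05 to 0.11 is plausible from one survey of 339 children before any trend error, but the article neither gives nor bounds it. Confidence is high in the method fault and lower in any particular figure.

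**What to change.** Replace the t-test with an estimate: the mean observed-minus-expected difference, or the observed/expected ratio, for 2015-2017. Take its confidence interval from a bootstrap that resamples the survey and follow-up children and re-fits the expected model in every replicate. Draw each child's 2015 and follow-up records together, so that the shared baseline is respected. Where individual records of an earlier survey are unavailable, add the model's standard error to the variance by another stated route.

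Make the adjustment for oral hygiene and sugar consumption through a regression model, for example of the child-level observed-minus-expected increment, to the extent that these variables were recorded, and say where they were not. Name 2015-2017 as the primary comparison and treat 2015-16 and 2016-17 as secondary. State whether the test is one- or two-sided.

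If children can be linked between the 2012 and 2015 surveys, one joint count model of pre- and post-intervention intervals is an option. The article does not establish that linkage, and such a model would change the planned comparator, so it should not be the default.

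The cost is a revised Analysis section, some programming and usually a wider interval. The bootstrap captures sampling error in the fitted model but not a wrongly chosen trend, so the interval remains conditional on the form of the model.

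### Partial attendance cannot show the most appropriate frequency: year-1-only children add nothing on frequency, and the one remaining contrast is self-selected

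*Protocol article*

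**What the plan says.** All statements are in the Methods of the protocol article.

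- **No assigned comparison group** (Study design): "As it is unethical to withhold any proven intervention from any child, no control group will be created". The same section adds: "Children who do not consent to participate may be natural controls if they consent to a dental examination at the end of the study".
- **Who is examined at the start** (Study design): "All consenting children will undergo a detailed head, neck and dental clinical examination and complete a questionnaire".
- **What happens at each return** (Study design): "all participating children will be invited to return for a dental examination, treatment of new incident disease and repeat of the prevention regime". The Intervention section gives the same order: examination, then treatment, then the preventive application.
- **Main outcome** (Analysis): "Dental caries increment (incidence) will be the main outcome measure used to determine the effectiveness of the preventive intervention". It is compared with an increment modelled from the 2004, 2012 and 2015 surveys.
- **Partial attenders** (Analysis): besides full participants, the plan names "those with baseline and only a year 1 follow-up, those with baseline and only a year 2 follow-up". These groups are expected to "further inform us on the most appropriate frequency of this preventive strategy".
- **Handling** (Analysis): "Both a group and matched analysis will be conducted to account for children who receive only part of the intervention". The Covariates section names oral hygiene behaviours and sugar consumption for adjustment.

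**The concern.** How often to apply the regimen is the practical question behind the study. The Background argues that two to four applications a year cannot be sustained in remote communities, and that evidence on less frequent schedules is lacking. A statement from this study about the most appropriate frequency would therefore be used, even as a secondary result.

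Two features make the statement doubtful. First, a group informs on frequency only if its members had a different number of applications before a comparable examination. Whether that is so depends on the order of events within a visit. Second, nobody is assigned to miss a visit. Whatever leads a family to miss one may also bear on caries, in either direction.

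A related question arises for non-consenters. An increment needs two examinations of the same child, and the plan describes only one for them.

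**Working it through.** The plan gives no figure on this point, so there is nothing to reproduce. The check counts exposures from the stated visit sequence.

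**Inputs.** Baseline is 2015, the year-1 follow-up 2016 and the year-2 follow-up 2017 (Analysis, from the intervals listed there). Each visit runs examination, treatment, application (Study design, Intervention). An application can affect only examinations that come after it, so applications before the last examination = number of attended visits earlier than the last one.

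| Group | Visits attended | Applications before last examination | Interval observed |
|---|---|---|---|
| Full participants | 2015, 2016, 2017 | 2 | 2 years |
| Baseline and year 1 only | 2015, 2016 | 1 | 1 year |
| Baseline and year 2 only | 2015, 2017 | 1 | 2 years |
| Non-consenters | one examination at the end | 0 | none |

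**Year-1-only children.** At the 2016 examination full participants also have one application and one year behind them. Exposure is identical. The second application to year-1-only children follows their last examination, so no outcome reflects it. Matching cannot create a difference in exposure that does not exist.

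**Year-2-only children.** Over 2015-2017 they have one application against two. Timing allows this contrast. Two things differ besides the number of applications:

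- who chose to attend in 2016;
- treatment of new disease, which full participants received at the middle visit.

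**Range of frequencies.** No group receives more than one application a year, so nothing more frequent than annual can be assessed.

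**Non-consenters.** One examination gives caries experience at one time. An increment is a difference between two examinations, so none can be formed from the examination described.

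**Illustration of sensitivity to selection, on assumed inputs.** The documents give no participation or attendance rates for this study. Assume:

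- 70% of the 600-650 invited children take part: 0.7 × 600 = 420 and 0.7 × 650 = 455;
- half attend fully: 210 and 228;
- 10-30% are year-2-only: 42 to 136;
- the second application has no true effect;
- a difference of d standard deviations in caries risk remains between the groups after matching and adjustment, in either direction.

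With SE = √(1/n₁ + 1/n₂), the chance of a two-sided p < 0.05 is Φ(d/SE − 1.96) + Φ(−d/SE − 1.96).

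- Smallest case, d = 0.2: SE = √(1/42 + 1/210) = 0.169; d/SE = 1.183; Φ(−0.777) + Φ(−3.143) = 0.219.
- Largest case, d = 0.2: SE = √(1/136 + 1/228) = 0.108; d/SE = 1.846; Φ(−0.114) + Φ(−3.806) = 0.455.

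| Residual selection difference d | Chance of p < 0.05 with no frequency effect |
|---|---|
| 0 | 5% |
| 0.1 SD | 9-15% |
| 0.2 SD | 22-45% |
| 0.3 SD | 43-79% |

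This shows only that modest residual selection would be enough to mislead. It does not estimate how much there will be.

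**The case against.** The protocol's wording is modest. Non-consenters are mentioned only as possible controls, and partial attenders are to add information rather than settle anything. The aims and hypotheses pose no frequency question. The hypothesis test compares observed with modelled increments, and nowhere says that non-consenters enter it or that an increment will be computed for them. A matched analysis is planned, hygiene and diet are adjusted for, and the choice of matching variables can properly be left to a fuller document.

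Most of this stands, and it rules out three stronger readings that a reader might infer:

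- **That timing defeats every frequency comparison.** It does not. The year-2-only group, which the plan names, gives a genuine two-versus-one contrast, and the objection to that contrast is selection and mid-study treatment.
- **That the main comparison is damaged by the lack of a baseline for non-consenters.** It never uses them.
- **That full attendance must look better than it is.** The documents do not show which way selection runs. Less engaged families might miss visits and have more caries, or children with more disease might attend more because visits include treatment.

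The objection does not rescue the frequency statement. Matching and adjustment cannot give year-1-only children a different exposure, and for year-2-only children they address only what was measured.

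**Conclusion.** The point holds as a limit on a secondary claim. Of the two partial-attendance groups named, one carries no frequency information and the other supports a single contrast, two applications against one over 2015-2017, that is confounded by self-selection and by treatment at the middle visit. A conclusion about the most appropriate frequency is more than this can bear. Non-consenters examined only at the end can be compared on caries experience but not on the main outcome.

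The exposure counts rest on the visit order stated in the protocol and need no further assumption. The size and direction of bias in the remaining contrast are unknown, and the percentages in the illustration depend wholly on assumed inputs. The effectiveness comparison with modelled increments is not affected by this point.

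**What to change.** In the Analysis section:

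1. Remove the statement that partial attendance informs the most appropriate frequency.
2. Limit the frequency contrast to the 2015-2017 increment in full participants against baseline-and-year-2-only children. Match or adjust for age, baseline caries, residential history of fluoridated water, and baseline hygiene and diet. Label it exploratory, and state that the groups also differ in treatment at the middle visit.
3. Use baseline-and-year-1-only children only in the 2015-2016 increment.

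In the Study design section, state that any data from non-consenters will be reported as an age-adjusted, exploratory cross-sectional comparison at the end of the study.

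The baseline items needed are already collected from participants under Study design, so the cost is revised wording and a weaker claim on frequency. No extra visits or examinations are required.
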